### 11.4.3 Goldmann Visual Field (GVF)

GVF results [52] will be interpreted and quantified independently by researchers at Johns Hopkins University, using a method described in Dagnelie [53] and used extensively in RP. The observed GVF and log transformation of GVF, as well as their respective change and percent change from baseline for the large (V4e) and smaller (III4e and I4e) targets will be summarized for all subjects using descriptive statistics (mean, standard deviation, minimum, median, and maximum).

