## **4.2 Discussion of Study Design**

The efficacy variables being used for this study are intended to generate results that are relatively stable over the very short time period during which each subject is treated during the study (7 days) and should therefore only change if there is a treatment effect. Subjects will be followed up for at least 12 months after treatment to assess the duration of treatment effect, as well as any potential delayed treatment effect. In preliminary data from this study, beneficial treatment effects have been observed in some subjects in at least 1 vision function measurement, but the duration of treatment effect is unclear, as is the timing of the onset of treatment effect [48]. Beneficial treatment effects need to be clear and clinically relevant if the treatment is to be developed further. The study does not include a control group, so each subject's baseline visual function will serve as the control for that subject.

Each subject will undergo daily treatments for 7 days, as it is believed that it will take at least 7 days for adequate amounts of QLT091001 and its precursor 9-*cis*-retinol to accumulate in the retina. However, a visual acuity test using best-corrected ETDRS is planned 24 hours after the first dose to evaluate whether a clinical effect of treatment occurs more rapidly.

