### **4.2.1 Rationale for Selection of Vision/Efficacy Tests**

No single test has been validated to definitively evaluate the response of treatment for LCA or RP. One potential benefit of the vision tests selected for this study will be identification of a primary endpoint for subsequent trials, if a beneficial treatment effect is observed.

While ERG testing is the gold standard for evaluating therapeutic levels of several experimental therapies and is used routinely to diagnose and monitor progression of most inherited retinal diseases including LCA, ERG testing has not yet been correlated with endpoints accepted by regulatory agencies, such as ETDRS vision and Humphrey Visual Field Analyzer (HFA). A limitation of full-field ERG is that the recording is a massed potential from the whole retina. Unless 20% or more of the retina is affected with a diseased

state, ERG recordings are usually normal (e.g., a legally blind person with macular degeneration, enlarged blind spot or other central scotomas has normal global ERGs). Most LCA and RP subjects have virtually no measurable ERG recordings, yet many of these subjects can still see, some quite well. Recent gene therapy trials for LCA have not reported changes in full-field ERG results because the methods in these trials treated less than 10% of the retina, so the ERG results would not be expected to change.

A method for quantitative analysis of Goldmann visual field (GVF) is being developed and has shown promise as an endpoint in subjects with LCA and RP in the current study, as described in the IB. (GVF has been used instead of HFA because HFA is usually not appropriate for young subjects and subjects with very low vision.) This GVF analysis is incorporated into the study for assessment as a potential primary endpoint for future trials (see [Section 11.4](#)).

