## **6 RANDOMIZATION AND MASKING PROCEDURES**

The study is not randomized or masked.

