### 9.5.3 Visual Field Tests

Visual field tests may be done at the visit days indicated in Table 3. Because these tests can be unreliable and difficult to perform if the subject has poor or no ability to fixate, these tests will be done only if the Investigator judges the subject capable and willing to undergo the test.

All visual field tests will be performed by appropriately certified and experienced study personnel. These tests include a psycho-physical component, so testing will incorporate each subject's learning curve, and intratest variability may be assessed. The methods that may be used are Goldmann, Humphreys, or microperimetry. At each applicable study visit, at least 1 of these 3 visual field tests, as appropriate for the subject, should be done. If more than 1 test is done, they should be done in the order listed above, with microperimetry done on a separate day. **For each individual subject, the test(s) done at follow-up visits must be the same as the test done at screening/baseline.** Refer to the RET IRD 01 Procedure Manual for complete instructions for visual field tests.

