## **11 STATISTICAL CONSIDERATIONS**

### **11.1 Sample Size**

The sample size of 28 subjects with LCA or RP caused by *RPE65* or *LRAT* mutation (up to 14 subjects for each disease cohort) will result in 7 subjects per genotype subgroup per disease cohort. This number is based on the small population of these LCA and RP genotypes and on clinical judgment that this is a sufficient number of subjects to meet the objectives of the study.

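### The protocol declares the study unmasked without exception and makes no provision for masking the outside Goldmann field readers to visit

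*Protocol*

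**What the plan says.** Section 11.4.3 says that GVF results will be "interpreted and quantified independently" by researchers at an outside university. It cites a published conversion method and describes it as in wide use in RP. The summaries cover observed and log-transformed GVF and their "change and percent change from baseline for the large (V4e) and smaller (III4e and I4e) targets", using descriptive statistics only.

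Section 6 consists of one sentence: "The study is not randomized or masked".

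Section 4.2 states: "The study does not include a control group, so each subject's baseline visual function will serve as the control for that subject".

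Section 4.2.1 describes the quantitative GVF method as under development, reports encouraging results from the current study, and adds: "This GVF analysis is incorporated into the study for assessment as a potential primary endpoint for future trials".

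Section 9.5.3 says of visual field testing: "These tests include a psycho-physical component". It also acknowledges a learning curve, and leaves the full test instructions to the Procedure Manual.

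**The concern.** Independence and masking are different safeguards. An outside reader has no stake at the site. If the record shows its visit, though, that reader still knows which field came before treatment and which came after. Section 11.4.3 has the readers interpret the fields as well as quantify them, so some judgment may enter. The only masking statement in the protocol leaves this route open.

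In a randomized comparison, a reading habit shared by both arms would largely cancel. Here there is one arm, and the reported quantity is the difference between later and baseline readings. A systematic difference in how the two are read looks the same as a treatment effect. What is at stake is less a conclusion of this study, which names no primary endpoint and sets no success rule for GVF, than the choice of endpoint for the next trials.

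**Working it through.** **1. Figures in the plan.** No figure in the protocol bears on reader error. The one stated design figure is the sample size: Section 11.1 says that it "will result in 7 subjects per genotype subgroup per disease cohort", and 2 diseases × 2 genotypes × 7 = 28, which reproduces the stated total. There is no power calculation, standard deviation or effect size to check against.

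**2. The sections side by side.**

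| Question | Where | What is fixed |
|---|---|---|
| Is anyone masked? | Section 6 | No; no exception named |
| Who reads GVF? | Section 11.4.3 | Outside researchers, independently |
| Are readers masked to visit? | Section 11.4.3 | Not provided for |
| What is the control? | Section 4.2 | Each subject's own baseline |
| What is reported? | Section 11.4.3 | Change and percent change from baseline |
| What is it used for? | Section 4.2.1 | Assessing GVF as an endpoint for later trials |

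These statements do not contradict one another. Together they permit reading with knowledge of visit, in a comparison that has nothing to absorb the result.

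**3. How a reading shift would pass through.** Let the true proportional change in area be g, and let post-treatment areas be read a fraction b too large while baseline is read correctly. The observed proportional change is

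(1 + g)(1 + b) − 1 = g + b(1 + g).

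The bias is b(1 + g). It equals b only when g = 0, and it is slightly larger than b when there is a true gain.

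**4. Illustration with assumed values and no true effect (g = 0).**

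- Error in area: b = 5% or 10% appears as a 5% or 10% gain.
- Error in isopter radius r, with area taken as proportional to radius squared, so b = (1 + r)² − 1:

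| Assumed radius error | Apparent area gain | Apparent change in log10 area |
|---|---|---|
| 2% | 1.02² − 1 = 4.0% | 0.017 |
| 5% | 1.05² − 1 = 10.3% | 0.042 |
| 10% | 1.10² − 1 = 21.0% | 0.083 |

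The log10 column is a plain change. Percent change in log GVF, which is also reported, depends on the baseline value and has no single figure. The squared-radius step is an approximation, and a conversion to solid angles would give other values for large fields.

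**5. Effect of sample size.** With independent subjects and a fixed standard deviation, going from 7 to 28 subjects halves the standard error (√(28/7) = 2). The bias b(1 + g) contains no n, so more subjects or eyes do not reduce it.

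**The case against.** The strongest reply is that this is silence and not an error. In a single-arm open-label study, the sentence in Section 6 most naturally describes treatment. Reader workflow usually sits in a reading charter or procedure manual, and neither is shown here. Section 11.4.3 presents the method as published and widely used, and the title of its reference describes a geometric conversion, which leaves limited room for judgment. GVF is one of several measures and is summarized only descriptively. The larger exposure arises at the site, where subject and perimetrist both know that treatment has been given, and masked readers would still receive fields that carry that expectation and any learning.

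Most of this stands as a limit on the claim:

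- A reader might infer that the GVF readers do know the visit. The documents do not say so. They show only that no masking is provided for.
- A reader might infer that the GVF results are inflated by some 5% to 10%. Nothing supports that; the figures above are assumptions.
- A reader might infer that the primary endpoint of this trial is compromised. It names none; Section 4.2.1 speaks of later trials.
- A reader might extend the point to ERG. Section 11.4.2 defines amplitudes and peak times by explicit landmarks and names no outside reader, so there is no basis for it.

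What does not stand is that the matter can simply be left to another document. Section 6 is the protocol's own masking section and excepts no one. If a charter does mask the readers, Section 6 is incomplete as written. If none does, an analysis plan written later cannot restore masking once fields have been read.

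**Conclusion.** The point holds as a cheap improvement to a design statement. The protocol declares no masking and provides none for the outside GVF readers, in a comparison where baseline is the only control. Any reader expectation about post-treatment fields would therefore pass uncancelled into the change from baseline. Whether such expectation operates, and how large it would be, cannot be determined from the documents. The conclusion rests on two readings: that *independently* does not itself mean masked, and that interpreting a field leaves some judgment to the reader. Open-label treatment is not in question, since masked reading is compatible with it.

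**What to change.** In Section 6, say that treatment is open-label but that GVF reading is masked. In Section 11.4.3, say that GVF records are stripped of subject and visit identifiers and sent to the existing external readers in random order, so that the readers are masked to subject and to pre- or post-treatment status. If a manual or charter already provides for this, refer to it in both sections.

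The cost is minor file handling: relabelling and shuffling before transfer, and keeping a linking key away from the readers. No new reader, visit or procedure is needed. The documents give no ground for requiring masking to genotype or disease cohort, because the comparison at risk is within subject, or for requiring that fields already quantified be read again.

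The change removes reader expectation only. Subject and perimetrist expectation and the learning effect acknowledged in Section 9.5.3 remain, and should still be stated as limits when GVF change is interpreted.

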## 11.4 Efficacy Variables and Analyses

Efficacy analyses will be performed on data from both eyes of all subjects included in the ITT data set. Each eye will be evaluated separately.

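### The planned mean percent change in observed Goldmann field area is biased upward in expectation, because each eye's noisy baseline is the denominator, and no control group carries the same bias

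*Protocol*

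**What the plan says.** Protocol section 11.4.3 lists the quantities to be reported for the V4e, III4e and I4e targets: observed GVF and its log, "as well as their respective change and percent change from baseline". These "will be summarized for all subjects using descriptive statistics (mean, standard deviation, minimum, median, and maximum"). Section 11.4 adds, for all efficacy variables, "Each eye will be evaluated separately". Read together, these make the arithmetic mean and SD of per-eye percent change in observed field area prescribed summaries. They stand beside the change in log GVF and the medians, and none is named as the one to be interpreted.

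Three other places bear on the point.

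- Section 4.2: "The study does not include a control group"; each subject's own baseline is the comparator.
- Section 4.2.1: "This GVF analysis is incorporated into the study for assessment as a potential primary endpoint for future trials".
- Section 9.5.3 says of visual field tests that "these tests can be unreliable and difficult to perform if the subject has poor or no ability to fixate". The statement is conditional on fixation, and testing is limited to subjects judged able to do it.

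The Protocol Summary and Table 3 (section 9.1) schedule visual field testing twice before treatment, at Screening and on Day -2/-1. Section 11.4.3 does not say whether one of these, or their average, is the GVF baseline.

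**The concern.** Percent change divides by the eye's own baseline. If that baseline reads low by chance, the percent change is inflated. If it reads high, the percent change is reduced, but by less. The two errors do not cancel in an arithmetic mean. The visible sign is that a loss cannot go below -100% while a gain has no upper limit. The cause is the noise in the denominator.

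In a controlled trial both arms would carry much the same bias, and a comparison would largely remove it. Here nothing can be subtracted, so a positive mean percent change could be taken for a drug effect on the measure being assessed as a primary endpoint for later trials. The mean percent change and the mean log change for the same eyes can also differ in sign.

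**Working it through.** **Inputs from the protocol.** Percent change in observed GVF, averaged arithmetically (11.4.3); eyes taken separately (11.4); no control group (4.2); two pretreatment field tests (Table 3). The protocol states no test-retest SD, power or effect size for GVF, so there is no figure of its own to reproduce.

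**Assumption.** Each test reads the true area multiplied by lognormal error with SD s on the natural-log scale, independently between tests. Because s is not in the protocol, a range of 0.1 to 0.5 is shown.

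**Step 1: a two-eye illustration.** One eye doubles and one halves. The percent changes are +100% and -50%, so the mean is (100 - 50)/2 = +25%. The mean log change is (ln 2 + ln ½)/2 = 0.

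**Step 2: single baseline, no true change.** With follow-up F and baseline B, ln(F/B) has mean 0 and variance 2s². Hence E[F/B] - 1 = exp(2s²/2) - 1 = exp(s²) - 1. For s = 0.3 this is exp(0.09) - 1 = +9.4%.

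**Step 3: baseline as the arithmetic average of the two pretreatment tests.** This was simulated; the result is close to exp(s²/2) - 1.

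| s (assumed) | Single baseline | Average of two tests | Mean log change (single baseline) |
|---|---|---|---|
| 0.1 | +1.0% | +0.5% | 0 |
| 0.2 | +4.1% | about +2% | 0 |
| 0.3 | +9.4% | +4.7% | 0 |
| 0.4 | +17.4% | +8.6% | 0 |
| 0.5 | +28.4% | +14.0% | 0 |

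The median percent change is also about 0 throughout. The bias does not depend on the lognormal form: additive normal error with a coefficient of variation of 0.1, 0.2 and 0.3 gives +1.0%, +4.6% and +12.8% with a single baseline.

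**Step 4: what a small group would show.** With 14 independent values, s = 0.3 and no true change, the simulated mean exceeds +10% in about 46% of studies and falls below -10% in about 6%. In 26% of studies the mean percent change is positive while the mean log change is negative. With the two pretreatment tests averaged, about 29% exceed +10%. At s = 0.1 with a single baseline, the mean is above zero in about 60% of studies, not far from the 50% that an unbiased summary would give.

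**Step 5: a true loss.** With s = 0.4, a single baseline and a true 10% loss, the expected mean percent change is 0.9 × exp(0.16) - 1 = 0.9 × 1.1735 - 1 = +5.6%.

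**Step 6: the log change needs a log-scale baseline.** If the two pretreatment areas are averaged on the area scale and then logged, the baseline is too high by about s²/4 in log units. This follows because ln of the average is about the average of the logs plus d²/8, where d is the difference of the two logs and E[d²] = 2s². At s = 0.3 the shift is 0.09/4 = 0.0225, so the mean log change would be about -2% under no effect. Averaging on the log scale leaves it at 0.

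**The case against.** The best defence is that the sentence already contains its own safeguard. It plans the change in log GVF, the absolute change and the median, so a reader would see a mean percent change that disagrees with them. Section 11.4 is wholly descriptive, with no test, threshold or primary endpoint, and choosing which summary governs can be left to an analysis plan not seen here. The size of the bias rests on an assumed SD, and the two pretreatment tests could both reduce the noise and let it be estimated.

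Much of this stands. The defect is confined to one statistic and its SD, and its size in this trial is unknown. What does not stand is that descriptive status makes it harmless. With no inferential analysis in section 11, these summaries are the only stated efficacy evidence, and the biased one has equal standing with the unbiased ones. Showing several summaries together does not say which to believe.

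A reader might also infer that section 9.5.3 concedes that GVF is unreliable in general. It does not. The statement applies to subjects with poor or no fixation, and the same section requires certified, experienced personnel and restricts testing to capable subjects.

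**Conclusion.** The point holds in a limited form. The planned arithmetic mean of per-eye percent change in observed GVF is biased upward in expectation under no true change. Under the assumed error model the bias runs from about +1% to +28% for s from 0.1 to 0.5 with a single baseline, and from about +0.5% to +14% if the two pretreatment tests are averaged on the area scale. It can be ignored near s = 0.1 and matters from about 0.2 to 0.3.

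Two stronger readings are not supported. One is that noise will produce a positive mean in this trial, or that a positive mean would be noise. The bias is an expectation, and any one sample can fall either way. The other is that the GVF analysis as a whole is unsound, whereas the log change and the median, both already planned, are free of this bias. The simulated frequencies for 14 values are illustrative. They assume independent values, which two eyes of one subject may not be, and section 11.4.3 pools all subjects, up to 28. The expected bias itself needs no independence between eyes, and a larger sample does not remove it.

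**What to change.** In section 11.4.3:

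- Replace the mean and SD of percent change in observed GVF with the back-transformed mean change in log GVF, 100 × (exp(mean ln change) - 1). This is a geometric mean ratio expressed as a percent.
- Name it as the GVF change summary to be interpreted.
- Keep the median, minimum and maximum of the individual percent changes as description.
- State which pretreatment test or tests form the baseline. If the two are averaged, average them on the log scale.
- State how eyes with zero area are handled. Log GVF and percent change both fail at a zero baseline, and log GVF also fails at a zero follow-up.

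A confidence interval is optional in a descriptive study. If one is given, it should allow for two eyes per subject.

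The cost is a few sentences in the protocol or analysis plan, with no new data, since the log change is already to be computed. The downsides are that the reported percentage will usually be smaller and that the zero-area convention has to be chosen and defended.

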***Sample Size and Statistical Analyses:***

The sample size of 28 subjects with LCA or RP due to RPE65 or LRAT deficiency is based on the small population of patients with these diseases and genotypes and on the clinical judgment that this is a sufficient number of subjects to meet the objectives of the study.

- AEs will be coded using the Medical Dictionary for Regulatory Activities (MedDRA) with the number and percentage of subjects experiencing an AE and the total number of events summarized by system organ class and preferred term.
- Concomitant medications will be coded with the World Health Organization Drug Dictionary and tabulated.
- Safety variables including laboratory tests, ophthalmologic examinations and procedures, and vital signs will be summarized with appropriate descriptive statistics by gene mutation subgroup, and disease cohort.
- ECG results, biomicroscopy, IOP, dilated fundus exam, height, and QLT091001 and metabolite levels (if available) will be listed by subject.
- ERG, BCVA scores measured by ETDRS testing, visual field tests, color vision, dynamic pupillometry, and nystagmus testing results will be summarized with appropriate descriptive statistics by gene mutation subgroup, and disease cohort.
- The subject questionnaire will be summarized with appropriate descriptive statistics by gene mutation subgroup, and disease cohort.

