### 11.4.1 Best-Corrected Visual Acuity Using ETDRS Testing

Visual acuity scores based on ETDRS testing and changes from baseline will be provided for each time point by gene mutation subgroup and disease cohort using descriptive statistics (mean, standard deviation, minimum, median, and maximum).

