### 11.4.2 ERG Variables

Analysis of the ERG will include variables of peak time and amplitude. The a-wave amplitude will be measured from baseline to trough and b-wave amplitude will be measured from a-wave trough to b-wave peak. Peak times will be measured from the flash onset to the peak of the wave under evaluation.

The responses of both eyes for each stimulus condition will be evaluated separately, and a- and b-wave amplitudes and implicit times will be measured in photopic and scotopic conditions to estimate the cone and rod contributions, respectively. B-wave amplitudes will then be plotted against the corresponding flash intensity in order to generate the photopic and scotopic luminance-response functions from which the rod and cone  $V_{\max}$ , retinal sensitivity ( $\log K$ ) and  $ka$  and  $kd$  (for the *Photopic Hill*) parameters can be calculated according to previously reported methods.

ERG variables and changes from baseline will be summarized by gene mutation subgroup and disease cohort using descriptive statistics (mean, standard deviation, minimum, median, and maximum). In addition, the a-wave and b-wave amplitudes will be presented graphically for each group by flash intensity.

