### 11.4.4 Other Efficacy Variables

Other variables (visual field [other than GVF], color vision, dynamic pupillometry, nystagmus testing, OCT, and FAF) will be summarized by gene mutation subgroup, disease

cohort, and visit using mean, standard deviation, median, minimum, and maximum for continuous variables; and counts and percentages for categorical variables.

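### Section 11.4.3 pools Goldmann visual field over all subjects, while the Protocol Summary promises visual fields by gene and disease

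*Protocol*

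**What the plan says.** The Protocol Summary, under Sample Size and Statistical Analyses, lists visual fields with the other efficacy tests: "visual field tests, color vision, dynamic pupillometry, and nystagmus testing results will be summarized with appropriate descriptive statistics by gene mutation subgroup", and also by disease cohort.

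The detailed statistical sections treat the efficacy variables as follows:

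- Section 11.4.1 (BCVA): scores and changes "will be provided for each time point by gene mutation subgroup and disease cohort using descriptive statistics".
- Section 11.4.2 (ERG): "ERG variables and changes from baseline will be summarized by gene mutation subgroup and disease cohort using descriptive statistics".
- Section 11.4.3 (GVF): observed and log-transformed values, with change and percent change, for three target sizes "will be summarized for all subjects using descriptive statistics (mean, standard deviation, minimum, median, and maximum"). No gene subgroup, disease cohort or visit is named.
- Section 11.4.4 (the rest, split by gene, by disease and by visit): "Other variables (visual field [other than GVF], color vision, dynamic pupillometry, nystagmus testing, OCT, and FAF) will be summarized by gene mutation subgroup, disease".

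Section 11.4 itself fixes the population for all of these: both eyes of every subject in the ITT set, each eye evaluated separately. Section 4.2.1 gives GVF a particular role. Its quantitative analysis is to be assessed as a potential primary endpoint for future trials.

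**The concern.** A reader who follows Section 11 as written would produce one GVF summary over everybody. A reader who follows the Protocol Summary would produce a summary for each gene subgroup and disease cohort. Both cannot be the plan.

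The variable affected is one that the protocol singles out for later use, and the protocol itself gives reasons why a pooled figure may mislead. Section 2.2 says that LRAT subjects may be less sensitive to treatment. Section 1.3.1 describes RP as initially much milder than LCA. Section 3 makes duration of improvement an objective, and a summary not tied to visits cannot address it. If response differs by gene or disease, a pooled mean dilutes the effect in the group that responds and hides the fact that the groups differ. A later trial that chose its endpoint or population from that table would be choosing from the wrong figure.

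**Working it through.** **Step 1: the plan's own figure.** Section 11.1 gives 28 subjects as 7 per genotype subgroup per disease cohort. 2 diseases × 2 genes × 7 = 28, so the figure reproduces. The design is built on four cells. No alpha, power, effect size or SD is stated, so no power calculation applies.

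**Step 2: can the passages be read together?** There are three possible routes.

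- *Section 11.4.4 covers GVF.* It does not: its bracket takes GVF out of the visual fields that it splits.
- *The phrase in Section 11.4.3 only names the population.* Section 11.4 has already set the population for every efficacy analysis, so on this reading the phrase is redundant. Section 11.4.3 would still name no breakdown, whereas Sections 11.4.1, 11.4.2 and 11.4.4 each name one.
- *The Protocol Summary governs.* Then Section 11.4.3 needs to say so. As it stands, the more detailed section is the one without the split.

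None of these removes the mismatch.

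**Step 3: the visit element.** The Protocol Summary does not mention visits for visual fields, and Section 11.4.2 does not mention them for ERG. The missing visit is therefore not part of the contradiction. It is a gap relative to Sections 11.4.1 and 11.4.4 and to the duration objective, and it can be closed in the same sentence.

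**Step 4: what pooling could do.** Let p be the share of RPE65 subjects among those with GVF data, and let m(RPE65) and m(LRAT) be the mean changes.

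Pooled mean = p × m(RPE65) + (1 − p) × m(LRAT).

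Take the extreme case m(LRAT) = 0, which is an assumption and not a figure in the protocol. The pooled mean is then p × m(RPE65):

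- p = 0.25: 25% of the RPE65 mean change
- p = 0.50: 50%
- p = 0.75: 75%

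At full planned enrolment p = 14/28 = 0.50. Section 5.1 sets only upper limits per cell, so the realised share is unknown and is shown as a range. A smaller difference between genes would dilute the result less.

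**Step 5: the price of splitting.** In SD units, taking one value per subject, the standard error of a mean is 1/√n:

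- n = 28: 0.189
- n = 14: 0.267
- n = 7: 0.378

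A full cell of 7 is twice as imprecise as the pooled 28 (0.378/0.189 = 2). BCVA and ERG already carry that price.

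**The case against.** The strongest reply is that this is one loose phrase. It may simply say who is included, the Protocol Summary's commitment is never withdrawn, and detailed table layouts usually sit in the SAP. The field data are collected either way, so a split can be produced later. Section 11.4.3 also asks for change, percent change and a log transformation, which partly deals with different starting severity.

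Much of this stands. It makes the point a matter of reconciling text and not a flaw in data collection. But two protocol statements that disagree are not the same as a detail left to the SAP. Scaling for baseline does not show a difference in response between genes. And a split first made after the data are seen carries less weight than one set beforehand.

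Three stronger readings are tempting but are not supported.

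- *Selection bias.* Section 4.2.1 says that the method "has shown promise as an endpoint in subjects with LCA and RP in the current study", so a reader might infer that pooling early and late subjects inflates the GVF result by a calculable amount. The protocol does not say how many subjects lay behind that statement. The 14 in Section 8.3 is a safety count and includes 2 at another dose level. Nothing says that GVF was picked as the best of several endpoints, and the origin is openly disclosed in a purely descriptive study. Splitting early from late subjects on top of gene and disease would leave 28/8 = 3.5 per cell on average, assuming an even split.
- *GVF left unmeasured.* Section 9.5.3 does not require Goldmann: "At each applicable study visit, at least 1 of these 3 visual field tests, as appropriate for the subject, should be done". But the choice depends on what suits the subject, Goldmann comes first in the test order, and Section 4.2.1 records that GVF has been used instead of Humphrey perimetry. The text shows a permission, not a loss of data.
- *An expected weaker LRAT response.* Section 2.2 calls this possible and does not predict it.

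**Conclusion.** The point holds as an inconsistency. The Protocol Summary splits visual fields by gene and disease, Section 11.4.3 does not split GVF, and Section 11.4.4 closes the route by which Section 11 could have restored the split. It is worth correcting because GVF is a potential future primary endpoint and the correction is nearly free.

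The size can only be illustrated. A pooled mean would show 25% to 75% of the RPE65 mean change, and 50% at full planned enrolment, on the assumption that LRAT subjects do not respond at all. No documented figure supports a more exact estimate. No hypothesis test or error rate is at stake.

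**What to change.** In Section 11.4.3, replace the all-subjects phrase with a summary by gene mutation subgroup, disease cohort and visit, and keep an all-subjects row if it is wanted for context. That brings the section into line with the Protocol Summary and matches the visit detail of Sections 11.4.1 and 11.4.4. The cost is one sentence and some further table rows. The drawback is small groups, up to 7 subjects per cell, so each cell should show its number of subjects.

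As an optional clarification only, Section 9.5.3 could name Goldmann as the method to use whenever a subject can perform field testing, with the other two methods as additions.
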